### Documentation

The investigator records the participation on a special identification list of patients. This list gives the possibility for a later identification of the patients and contains the patient number, full name, date of birth, and the date of the enrolment into the study. The identification list of patients remains in the study center after the closure of the study. It is the responsibility of the investigator to document all data of the clinical study correctly and completely into the database. Important harms or unintended effects will be recorded in each group.

### Dropouts and exclusion of the clinical trial

To account for 20% attrition during the study period (“dropouts”), it is planned to recruit 80 patients per study group (160 overall) at baseline (see section “Statistics”). If patients request *after* randomization on their own free will a different treatment method — for example, if a patient requests surgery in conservative group — they have to be excluded from the study.

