## Outcome parameters

### Patient-reported outcome

The Banff Patellofemoral Instability-Instrument (BPII) 2.0 was reported as valid, reliable, and responsive patient-reported outcome tool in the field of patellofemoral instability [48, 49] and is used in the validated German version [50]. The BPII 2.0 serves as one of two major outcome instruments (hypothesis 1).

For exploratory reasons, the following further patient-reported parameters will be assessed in both groups: As second disease specific score, patients accomplish the Kujala Score [51] which was quoted as a reliable, valid, and responsive tool for patellofemoral disorders [52, 53]. In addition, the Short-Form 12 is used (version 2, German; SF-12v2) [54] to determine the general health outcome and the Marx activity scale to rate a patient’s physical activity [55]. The Marx Score asks for the highest activity in the last year. For postoperative monitoring of a patient’s activity, a “modified version of the Marx Score” will be used that refers to the last 2 months.

All abovementioned outcome scores are self-administered and will be assessed preoperatively, 6 and 12 months postoperatively, and then yearly. Those scores are collected during routine visits at the hospital. Alternatively, the questionnaires for assessment of the outcome scores can be filled out online by the patients to reduce dropouts.

The follow-up period is planned for 2 years. However, with the patient’s consent, the period can also be prolonged.

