### Other outcome parameters

Recurrence rate is assessed as second major outcome parameter (hypothesis 2). To keep proper medical records on recurrent patella dislocations, the patients are interviewed by telephone on a monthly basis (in addition to the abovementioned visits at the hospital).

The apprehension test is assessed by an experienced observer during the abovementioned routine clinical visits (grade 0, no evasion; grade 1, slight evasion/avoidance; grade 2, gross evasion/avoidance; grade 3, patient too anxious to allow the test).

Joint degeneration is assessed preoperatively and every three years postoperatively by means of MRI (PD-FSE with fat-sat high-resolution in all three planes/T1-TSE, sagittal/T2 weighted, isotrope 3D sequence sagittal reformatted in all three planes). The semi-quantitative MRI Osteoarthritis Knee Score (MOAKS scoring) is applied to rate the degenerative changes determined by MRI [56]. The MOAKS scoring is determined by always the same experienced musculoskeletal radiologist. Additionally, TT-TG distance is measured on postoperative MRI.

In addition, the Patella Instability Severity Score is assessed for exploratory reasons [57].

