### Statistics

Patient characteristics will be presented as means, standard deviations, and percentages. The main analysis will use linear mixed models that allow data modeling with a varying number of assessments per patient and time-varying covariates. Such a model will be used to compare the differences in changes over time between the two study groups. The following terms will be included in the model: a random baseline, a first-order autocorrelation covariance matrix, a fixed-effect patient group, a fixed effect time point, and the group-by-time interaction (reflecting the intervention effect). The BPII 2.0 will serve as the primary outcome parameters. The main analysis is “intention to treat” and will focus on the group difference in the change of BPII 2.0 scores between pre-op and 2-year follow-up. The abovementioned secondary outcome parameters will be analyzed with the same model.

Power/sample size analysis was done for the comparison of the two study arms at a 2-year follow-up with regard to the BPII Score. As there are no specific minimal important difference (MID) for the BPII available from the literature, we defined the MID to be 0.5 standard deviations following general recommendations from the literature [58]. A sample size of N = 64 per study arm (128 overall) provides 80% power (alpha = 0.05, two-tailed) to detect a difference of 0.5 standard deviations in a t-test for independent samples. To account for 20% attrition during the study period (“dropouts”), we plan to recruit 80 patients per study group (160 overall) at baseline.

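### Excluding patients who ask for the other treatment after randomisation contradicts the intention-to-treat main analysis and probably favours the conservative arm

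*Protocol article*

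**What the plan says.** The protocol article, under Dropouts and exclusion of the clinical trial, deals with patients who, once randomised, request "on their own free will a different treatment method". Its example is: "if a patient requests surgery in conservative group — they have to be excluded from the study". The sentence follows directly after the 20% attrition allowance. It does not limit the rule to requests made before treatment starts, does not say that excluded patients remain in follow-up, and does not say what happens to data already collected.

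Under Statistics: "The main analysis is “intention to treat” and will focus on the group difference in the change of BPII 2.0 scores", measured from pre-op to 2 years. The model is one of the "linear mixed models that allow data modeling with a varying number of assessments per patient and time-varying covariates".

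Under Patient-reported outcome: "The follow-up period is planned for 2 years". Under Other outcome parameters, recurrence has equal standing with the BPII 2.0 as a major outcome: "Recurrence rate is assessed as second major outcome parameter (hypothesis 2"). It is tracked by monthly telephone interview in addition to the hospital visits.

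**The concern.** Intention to treat keeps every randomised patient in the allocated arm, whatever treatment the patient later wants or receives. A compulsory exclusion triggered by a treatment request does the reverse. A separate analysis plan could not fully repair this, because a patient who has left the study has no 2-year BPII 2.0 score and no later recurrence record to analyse.

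The selection is unlikely to be neutral. The wording covers both arms, so a surgical-arm patient who declines the operation is excluded too. But a completed operation cannot be exchanged for conservative care, so requests made later in the 2 years must come almost entirely from the conservative arm. The patients likeliest to ask are those who re-dislocate or whose knee stays unstable. If so, the rule removes poor outcomes from one arm, on both major outcomes. This mechanism is an inference, though a likely one. The protocol does not state it.

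**Working it through.** **1. The plan's own figure.** Inputs from Statistics: difference 0.5 SD, two-sided alpha 0.05, 80% power, 20% attrition. The exact two-sample t-test needs 63.77, so 64 per arm, with 80.1% power. Recruitment is 64 / (1 − 0.20) = 80 per arm, 160 overall. The stated sample size reproduces and is not in dispute.

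**2. The two rules side by side.** Take a conservative-arm patient who re-dislocates at month 9 and asks for surgery. The exclusion rule ends participation at month 9. Intention to treat requires the 2-year BPII 2.0 and all recurrences up to 2 years, counted in the conservative arm. No passage reconciles the two.

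**3. Worst-case illustration.** The documents give no crossover rate and no expected recurrence rate, so every input here is an assumption:
- conservative 2-year recurrence p = 0.30
- share of recurrers who request surgery q = 0.5
- recurrers score 0.8 SD below non-recurrers
- no exclusions in the surgical arm
- no data from excluded patients are used

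*Recurrence.* Excluded share = pq = 0.15. Observed rate = p(1 − q) / (1 − pq) = 0.15 / 0.85 = 17.6%, instead of 30%. Whatever the surgical-arm rate, the observed risk difference moves by 30 − 17.6 = 12.4 points. At p = 0.30, q of 0.25, 0.5 and 0.75 gives 24.3%, 17.6% and 9.7%.

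*BPII 2.0.* Set the full conservative mean to 0 and the surgical mean to +0.5. Non-recurrers are then at 0.30 × 0.8 = +0.24 and recurrers at 0.24 − 0.8 = −0.56. Mean of those left = (0.70 × 0.24 − 0.15 × 0.56) / 0.85 = 0.084 / 0.85 = 0.10. Apparent effect = 0.5 − 0.10 = 0.40 SD. With 64 and 64 × 0.85 = 54.4 patients, t-test power is 57.8%. Over p = 0.20 to 0.40 and q = 0.25 to 0.75, the effect is 0.47 to 0.29 SD and power 73% to 32%.

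**4. What intention to treat gives on the same inputs.** The 15% stay in the conservative arm after having surgery.
- If they reach the surgical mean: conservative mean = 0.084 + 0.15 × 0.5 = 0.159, effect 0.34 SD, power 48% with 64 per arm.
- If they reach the non-recurrer level: 0.084 + 0.15 × 0.24 = 0.12, effect 0.38 SD, power 57%.

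Neither is better than the 0.40 SD and 58% under exclusion.

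**5. Check with a second model.** Suppose a fraction f of the conservative arm is excluded, and the tendency to request the switch correlates r with a poor outcome. The remaining mean rises by r·φ(z_f) / (1 − f), where z_f is the f-quantile of the standard normal distribution and φ its density. For r = 0.3 to 0.5, a true 0.5 SD appears as 0.44 to 0.40 SD at f = 0.10, and as 0.40 to 0.33 SD at f = 0.20. With no true difference, using standard error √(1/64 + 1/(64(1 − f))), the two-sided error is about 6% to 8% at f = 0.10 and 9% to 15% at f = 0.20, instead of 5%.

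**The case against.** **The mechanism is not documented.** The rule speaks of a free choice by the patient. It mentions neither re-dislocation nor persistent instability, and it also catches patients who refuse their allocation soon after randomisation, before any outcome exists. Whether surgery indicated after a recurrence counts as such a request is not stated. This stands: the direction of the bias is likely, not proven, and surgical-arm refusals would add selection of their own.

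**Data collected before exclusion may survive.** Monthly calls would normally record a recurrence before the request that follows it, and a mixed model can use earlier BPII 2.0 scores. This also stands in part, because the text neither keeps nor discards such data; the illustration is therefore a worst case. But a re-dislocation and request between two visits may leave no score that shows the failure, and the 2-year score and later recurrences are lost either way.

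**Two stronger readings are tempting.** A reader might infer that these exclusions come on top of the 20% attrition allowance and leave the trial short of patients. The protocol does not support that: allowance and rule stand together in one paragraph on dropouts and exclusion, and the natural reading is that the 20% may include them. A reader might also infer that keeping switchers restores the planned 80% power. It does not, as step 4 of the working shows.

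**Conclusion.** The contradiction stands on the text alone and needs no calculation: exclusion on request and an intention-to-treat main analysis cannot both be carried out. It should be corrected, because follow-up that is never collected cannot be recovered.

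The exclusion is probably informative and arm-dependent, and would probably flatter conservative care on both major outcomes. Its size cannot be derived from the documents. The 17.6% observed recurrence and the 0.40 SD effect rest wholly on the assumptions listed in step 3, including one-arm exclusion and full loss of the excluded patients' data.

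The argument for the change is validity, not power. Dilution under intention to treat is a known property of a treatment-policy estimate, and it does not create a difference where the treatments are equivalent. Selective removal can, as the raised error rates in step 5 illustrate.

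**What to change.** Reconcile the two sections by replacing the exclusion sentence under Dropouts and exclusion of the clinical trial. The replacement should say:
- patients who request or receive the other treatment remain in the study, with BPII 2.0 and recurrence followed to 2 years;
- they are analysed in the arm to which they were randomised;
- the date of and reason for each switch are recorded;
- only withdrawal of consent for data collection ends follow-up;
- any analysis without switchers is a labelled sensitivity analysis.

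This concerns data retention and analysis only. It does not bear on which treatment such a patient should receive.

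The cost is small: one sentence of protocol text and a log of switches. The visits and monthly calls are already planned. The downside is that the result estimates the effect of a treatment policy, diluted by crossover, and should be reported as such.

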### Interventions

In both groups, in case of relevant hemarthrosis and danger of skin or soft tissue exposure, a joint aspiration is performed [46].

### Conservative group

In the conservative group, patients use a motion-restricting knee brace that (a) protects the patella from lateralization and (b) limits knee range of motion. The range of motion limitation is set to 0-20-40° for week 1-2, 0-10-60° for week 3–4, and 0-0-90° for week 5-8. Partial weight-bearing is applied for week 1 and 2. Patients are prescribed outpatient physical therapy following a protocol suggested earlier by the “Patellofemoral Committee of the German-Speaking Arthroscopy Society (AGA)” [46]:
*Phase 1 (week 1 + 2)*. Range of motion 0-20-40°, partial weight-bearing*Phase 2 (week 3 + 4)*. Range of motion 0-10-60°, progression to full weight-bearing, emphasis on quadriceps recruitment (especially vastus medialis)*Phase 3 (week 5–8)*. Range of motion 0-0-90°, re-acquiring activities of daily living, core stability, sensorimotor training (leg axes stabilization), strength training*Phase 4*. Return to sports, dependent on the type and previous level of sports activity, gradual increase of training volume and intensity

### Surgical group

The surgical treatment is performed in a tailored manner, addressing the respecting pathologic anatomy that predisposes to LPD. MPFL reconstruction is performed in every patient. Other surgical techniques listed below will be applied in individual combinations, dependent on patient’s needs.

### MPFL reconstruction

#### MPFL reconstruction is applied in all patients of the surgical group

MPFL reconstructionhas been reported with a high variety of surgical techniques (graft type, single vs. double bundle, type of fixation, etc.). The specific surgical technique is carried out on surgeon’s preference at the respective center of the multicentric study.

### Trochleoplasty

Deepening trochleoplasty will be carried out in those patients of the surgical group who suffer from high-grade trochlea dysplasia.

### Tibial tuberosity transfer

Medializing TTT will be applied to those patients with TT-TG distances ≥ 18 mm in the MRI. Distalizing TTT will be applied in patients with Caton-Deschamps Index > 1.2 [47].

### Derotational osteotomy

In those patients with femoral antetorsion ≥ 40° (n. Waidelich/Strecker), a distal femoral derotational osteotomy is carried out. The precise surgical technique for that procedure is given over to the surgeon of the respective center.

### Varus osteotomy

In patients with valgus clinical appearance, a weight-bearing long-standing x-ray should be performed to precisely assess the degree of the deformity in the frontal plane (mechanical femorotibial angle).

In cases with a mechanical femorotibial angle > 5°, a varus osteotomy is performed at the location of the deformity.

Applying a “pragmatic” surgical approach, *not each* single pathology in the patient’s anatomy is addressed. Instead, a maximum of 3 surgical techniques (including the MPFL reconstruction) are performed in one patient. This means, that the 3 leading pathologies are surgically addressed, even in the rare case that 4 or more surgical techniques could be considered. In this sense, lateral release or lateral lengthening and arthroscopy are — for this protocol — not counted as distinct techniques.

## Outcome parameters

### Patient-reported outcome

The Banff Patellofemoral Instability-Instrument (BPII) 2.0 was reported as valid, reliable, and responsive patient-reported outcome tool in the field of patellofemoral instability [48, 49] and is used in the validated German version [50]. The BPII 2.0 serves as one of two major outcome instruments (hypothesis 1).

For exploratory reasons, the following further patient-reported parameters will be assessed in both groups: As second disease specific score, patients accomplish the Kujala Score [51] which was quoted as a reliable, valid, and responsive tool for patellofemoral disorders [52, 53]. In addition, the Short-Form 12 is used (version 2, German; SF-12v2) [54] to determine the general health outcome and the Marx activity scale to rate a patient’s physical activity [55]. The Marx Score asks for the highest activity in the last year. For postoperative monitoring of a patient’s activity, a “modified version of the Marx Score” will be used that refers to the last 2 months.

All abovementioned outcome scores are self-administered and will be assessed preoperatively, 6 and 12 months postoperatively, and then yearly. Those scores are collected during routine visits at the hospital. Alternatively, the questionnaires for assessment of the outcome scores can be filled out online by the patients to reduce dropouts.

The follow-up period is planned for 2 years. However, with the patient’s consent, the period can also be prolonged.

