## Methods

### Study design and participants

A prospective, randomized-controlled trial design is applied. Before commencement of the study, approval of the ethical committees (EC) of the participating centers is obtained. Patients with objective, unilateral first time LPD, based on patient’s history and physical examination, will be considered for participation. After written informed consent the patients are included in the study at their first visit at the emergency department. Excluded are (a) patients with osteochondral lesions requiring removal/refixation, (b) patients with recurrent LPD, (c) pregnant patients, and (d) patients > 45 years of age and patients with physical maturity Kramer stage 1 to stage 3a [44, 45].

Clinical workup includes thorough history, physical evaluation, plain radiographs, and magnetic resonance imaging (MRI) in all patients. When the physical examination reveals suspicion of maltorsion syndrome, MRI (or CT scan) is done of the hip, knee, and ankle to quantify femoral and tibial torsion. When the physical examination reveals suspicion of a relevant genu valgum or varum a long-standing x-ray is performed.

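### The scores, clinic visits and MRI, and the start of the primary BPII 2.0 change, are timed by the operation, which the conservative arm never has; its time origin is undefined, and the surgical arm is timed from an event after randomisation.

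*Protocol article*

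**What the plan says.** Under Patient-reported outcome, the article first lists the BPII 2.0 as a major outcome and then says that "the following further patient-reported parameters will be assessed in both groups". It closes with one timetable for the whole set: "All abovementioned outcome scores are self-administered" and "will be assessed preoperatively, 6 and 12 months postoperatively, and then yearly". No separate timetable is given for either arm.

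Under Statistics, the intention-to-treat main analysis "will focus on the group difference in the change of BPII 2.0 scores between pre-op and 2-year follow-up". The model contains "a random baseline, a first-order autocorrelation covariance matrix, a fixed-effect patient group, a fixed effect time point, and the group-by-time interaction".

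Under Other outcome parameters, the apprehension test is done at the same clinic visits, and the MRI for joint degeneration is also scheduled before and after the operation. The monthly telephone interviews about re-dislocation carry no such anchor.

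On the arms themselves: "In the conservative group, patients use a motion-restricting knee brace", together with physical therapy. The section on dropouts removes a conservative patient who asks for surgery, so no operation date arises later in that arm either. On sequence: "After written informed consent the patients are included in the study at their first visit at the emergency department", and the Randomization section places allocation after inclusion. No interval from randomisation to surgery is stated.

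**The concern.** A change score needs a start and an end that mean the same thing in both arms. Here both are described relative to surgery. For conservative patients that rule cannot be applied, and no section supplies a substitute such as injury, inclusion or randomisation. Sites would have to improvise.

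For surgical patients the rule can be applied, but its anchor comes after randomisation. A score completed on the eve of surgery complies with the text, although by then the patient knows the allocation and the acute injury may have begun to settle. The randomised comparison is protected only if the baseline precedes allocation, or at least is taken at the same point in both arms.

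The planned model does not repair this. The pre-operative score is one of the modelled time points, and the effect of interest is the group-by-time interaction, so a group difference that arises at the first time point is subtracted from the difference at two years. Time enters as a fixed effect of nominal visit, which cannot correct for unequal elapsed time behind the same visit label.

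**Working it through.** **1. Which anchors apply to which arm**

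| Item | Anchor in the article | Surgical arm | Conservative arm |
|---|---|---|---|
| Baseline scores | before the operation | defined only as some time before surgery | undefined |
| 6 and 12 months, then yearly | after the operation | defined | undefined |
| Start of the primary change | pre-operative score | as for baseline | undefined |
| MRI | before and every three years after the operation | defined | undefined |
| Monthly recurrence calls | none stated | start not stated | start not stated |

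The Hypotheses section (two years), the planned 2-year follow-up period and the use of the word baseline in Statistics give no origin that would fill the last column. By design 80/160 = 50% of recruited patients have no operation date.

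**2. The plan's own figures**

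Inputs from Statistics: difference 0.5 SD, two-sided alpha 0.05, power 80%, 20% attrition. The exact two-sample t-test needs 63.77, so 64 per arm, with power 80.1% at 64. Then 64/(1 − 0.20) = 80 per arm, 160 overall. Both figures reproduce, and neither depends on the time origin.

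**3. Unequal clocks (assumed waits)**

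The article gives no wait for surgery. Suppose the wait after randomisation is w months and conservative patients are timed from randomisation. A surgical visit labelled m months then falls at m + w months after randomisation, which is later by w/m.

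| Assumed w (months) | 6-month visit falls at | 24-month visit falls at |
|---|---|---|
| 0.5 | 6.5 (8% later) | 24.5 (2% later) |
| 1 | 7 (17%) | 25 (4%) |
| 2 | 8 (33%) | 26 (8%) |
| 3 | 9 (50%) | 27 (12.5%) |

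At the primary time point the displacement is small if the wait is short.

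**4. Shifted baseline (assumed shifts)**

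Let b be the improvement, in SD units, already present in the surgical baseline because it was taken later. The difference in change becomes (true effect − b): one-for-one.

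Taking the SD of change as σ√(2(1 − ρ)), it equals σ when ρ = 0.5. This is an assumption, as the article gives no correlation. With 64 per arm the standard error is √(2/64) = 1/√32, so a shift b moves the test statistic by b√32: 0.28 for b = 0.05, 0.57 for b = 0.10 and 1.41 for b = 0.25. The two-sided critical value on 126 degrees of freedom is 1.979.

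| Assumed b | Rejection rate, no true effect | of which against surgery | of which for surgery | True 0.5 SD benefit appears as | Power |
|---|---|---|---|---|---|
| 0 | 5% | 2.5% | 2.5% | 0.50 SD | 80% |
| 0.05 | 5.9% | 4.7% | 1.3% | 0.45 SD | 71% |
| 0.10 | 8.7% | 8.1% | 0.6% | 0.40 SD | 61% |
| 0.25 | 28.9% | 28.9% | under 0.1% | 0.25 SD | 29% |

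The values of b are chosen for illustration; 0.25 SD is half the stated minimal important difference. A surgical baseline that has partly recovered works against surgery: it does not make a false claim of surgical benefit more likely.

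**The case against.** The strongest reply is that the pre-operative label is loose wording for a baseline at inclusion. Patients enter at the emergency visit and are then randomised, a score taken at that visit is pre-operative in the literal sense, and Statistics itself uses the word baseline. This is a fair reading, and it defeats one stronger claim. A reader might infer that the surgical baseline is in fact taken after allocation and after a wait. The article permits that but does not require it, and it states no wait. The reply does not remove the point, because no section says that the scores are collected at inclusion, and the reading does nothing for the follow-up visits, which are still counted from the operation.

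A second reply is that visit tables and time origins belong in the full protocol, which an article condenses. That would answer a missing detail. Here the article does state the timetable and the primary contrast, in terms that cannot apply to half the sample.

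A third reply concerns recurrence. A reader might infer that re-dislocations between randomisation and surgery go uncounted, or that the surgical arm has a shorter risk window. The article does not support this: the monthly calls are not tied to the operation, and a two-year window counted from surgery would be displaced, not shortened. What stands is only that the article does not say when counting begins.

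Finally, the size of any bias is assumed throughout. That is correct, and the figures above show sensitivity, not an estimate.

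**Conclusion.** The point holds as a defect in how the primary change and the visit schedule are defined. The conservative arm's baseline and visit origin are undefined, and the surgical arm is timed from an event after randomisation, which leaves room for a post-allocation baseline in one arm and for unequal clocks. It does not hold as a demonstrated bias: the article gives neither the wait for surgery, nor the early course of the BPII 2.0, nor its correlation over time.

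Under the stated assumptions (64 per arm, SD of change equal to the SD of the score, shift in the surgical arm only), a baseline rise of 0.10 SD gives about 9% rejections under no effect, and 0.25 SD about 29%, almost entirely against surgery. The timing of the baseline matters more than the displacement of the 24-month visit. Correction is needed before recruitment, because a baseline score taken too late cannot be recovered afterwards.

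**What to change.** - Collect the BPII 2.0 and the other scores before randomisation in both arms.
- Define day 0 as randomisation for every patient.
- Schedule the 6-, 12- and 24-month assessments from day 0, and count re-dislocations from day 0, in both arms.
- In Statistics, replace the pre-operative starting point of the primary change by baseline, defined as above.

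The cost is wording in the protocol and the case report form. The article already allows online completion of the questionnaires, which makes visits timed from randomisation easier to keep. The sample size stays at 64 evaluable and 80 recruited per arm. The one drawback is that surgical patients are assessed slightly earlier after their operation than under a postoperative timetable, by the length of their wait.
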